
#### Exclusion criteria

The exclusion criteri are:The patients are undergoing current administration of anticancer therapies, or are attending other clinical trials.History or current evidence of brain metastasis, including leptomeningeal involvement.Patients with a BRCA mutation who have poor response to the therapeutic regimen.Patients with severe vascular diseases, including unstable angina, myocardial infarction, or severe arrhythmia in the past 6 months.History of HIV infection or active chronic hepatitis B or C.Patients with other serious infectious diseases.Patients positive for ER/PR/HER-2.Patients with allogeneic organ transplants requiring immunosuppressive therapy.History of other malignant tumors within 5 years, except for cured cervical carcinoma in situ or basal cell carcinoma of the skin.Other destabilizing factors (such as drug abuse and medical, psychological, or social conditions) that may interfere with patient compliance or have an impact on the trial results.Allergy to target drugs or allergy to related drugs applied in the trial.Pregnant or lactating women.

### Recruitment

Patients will be recruited based on their diagnosis at the Department of Breast Medicine, Liaoning Provincial Cancer Hospital in China, which has a sufficient number of patients with advanced breast cancer. Patients will be screened for eligibility by research staff to ensure all inclusion and exclusion criteria are met. The research staff identifying patients for inclusion into the study will be blinded to the study objectives.

### Randomization

A professional, independent statistician, who will not be involved in the recruitment process of the study, will randomize the participants. The statistician will use the Statistical Analysis System (SAS 9.1) software to generate a randomization sequence list, and assign each patient a serial number. Treatment allocations will be sealed in opaque envelopes prepared by research assistants who will not be involved in the recruitment process. These envelopes will be secured in a double-locked cabinet by another investigator who will not be involved in the trial.

### Blinding

The patients, investigators, and the statistician will be unaware of the treatment allocation until the end of the trial. The Office of Data Quality will provide the randomization assignment list to the Jiangsu Hengrui Pharmaceutical Co., Ltd., China, which will provide the blinded capsules. Nurses who will not participate in the trial will dispense drugs to eligible patients based on their allocation sequence.

In the case of an emergency, the investigators can promptly determine the medication that the patients are receiving, to ensure timely and correct medical treatment. If unblinding is necessary, study staff will contact the Office of Data Quality.

### Drug administration

Vinorelbine plus apatinib group: a 40 mg vinorelbine tartrate soft capsule (brand name Navelbine, registration number H20140657; Pierre Fabre Medicament, Boulogne, France) is administered orally in the morning (at least 1 h before, or at least 1 h after meals), three times a week (Mondays, Wednesdays, and Fridays), for a continuous 21-day cycle. A 500 mg apatinib mesylate tablet (brand name Aitan; state medical permission number. H20140103), is administered orally once a day for a continuous 21-day cycle.

Vinorelbine plus placebo group: oral administration of vinorelbine will be the same as in the vinorelbine plus apatinib group. In addition, the patients will be given oral placebo (starch as an ingredient). The placebo appearance, including shape, size, color and weight, taste, labeling, and packing is the same as that of the apatinib mesylate tablets.

The placebo and the apatinib will be manufactured by Jiangsu Hengrui Pharmaceutical Co., Ltd., China in accordance with the guidelines of Good Manufacturing Practice (Chinese Edition). The manufacturer will have no direct involvement in the study (apart from the drug manufacturing and delivery to the clinical trial centers). An assessment will be conducted at the end of every second cycle of the described administration protocol, until unacceptable toxicity or disease progression is observed.

### Dose adjustment

Principle for dose adjustment: in the case of adverse events associated with apatinib, the dose will be adjusted first (Table 2). There are two dose levels for apatinib: (1) initial dose: 500 mg, once daily; (2) secondary dose: 250 mg, once daily. Medication will be paused if the patients cannot recover from drug toxicity. The time for each pause and the cumulative time of overall pauses per cycle are limited to 1 week. There is a maximum of two pauses per cycle, to ensure the medication intensity in each patient. Patients not meeting the above criteria, or having a delay of the subsequent treatment cycle of at least 2 weeks, will be required to withdraw from the trial.

**Table 2 Tab2:** Principle for the adjustment of apatinib dose

Classification of adverse reactions	NCI-CTC level	Dose adjustment
Hematologic adverse reactions	3	Drug administration will be paused at level 3 and will be continued at the initial dose when the NCI level is restored to ≤ level 2. If NCI ≥ level 3 occurs again, drug administration at the secondary dose will be continued
	4	Drug administration will be paused at level 4 and will be continued at the secondary dose when the NCI is ≤ level 2
Non-hematologic adverse reactions	3	Drug administration will be paused at level 3 and will be continued at the initial dose when the NCI is restored to ≤ level 1. If the NCI ≥ level 3 occurs again, drug administration at the secondary dose will be continued
	4	Drug administration will be paused at level 4 and will be continued at the secondary dose when the NCI is ≤ level 1

Adverse reactions will be assessed using the National Cancer Institute Common Toxicity Criteria (NCI-CTC) Version 4^30^

The dose of apatinib can be adjusted at any time during each dosing cycle. Once the dose is reduced, however, a subsequent increase to the previous level is not permitted. Only a single dose adjustment is allowed for each subject. After the dose is decreased to 250 mg, no further dose adjustments are permitted for any reason. However, pausing of medication administration will still be permitted.

When any conditions that meet the criteria for drug withdrawal are observed, administration of vinorelbine will be discontinued. If the patient meets the criteria for drug re-administration in the subsequent cycles, vinorelbine administration will be resumed, but the doses that are not taken during the withdrawal period will be omitted (Table 3).

**Table 3 Tab3:** Criteria for drug withdrawal and re-administration

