**Fig. 1 Fig1:**
[figure not shown]
Standard Protocol Items: Recommendations for Interventional Trials (SPIRIT). Timepoint (t): -t1: baseline evaluations (conducted within 2 weeks of the start of protocol therapy); t0: random allocation; t1: during treatment (evaluations will be conducted every 6 weeks (two cycles)); t2: patients will be monitored for new or existing AEs at 4 weeks after treatment discontinuation; t3: follow up for survival will be monitored every 3 months after treatment discontinuation until patient death or study completion. *Eligible patients will be randomly assigned to receive either oral vinorelbine plus placebo (control group) or oral vinorelbine combined with apatinib mesylate (experimental group). ^a^ Concomitant medication includes opioid analgesics and new anticancer treatment. ^b^ Laboratory examinations include hematology (hemoglobin, white blood cell count, neutrophil count, and platelet count); blood biochemical tests (total bilirubin, alanine aminotransferase, aspartate aminotransferase, alkaline phosphatase, serum creatinine, total protein, Na^+^, K^+^, Mg^2+^, Cl^−^, Ca^2+^, urea, and pregnancy test (if applicable); and tumor marker detection (breast cancer-associated antigen CA153 and carcinoembryonic antigen). ECOG PS, Eastern Cooperative Oncology Group performance status; EORTC QLQ-C30, the European Organization for Research and Treatment of Cancer Quality of Life Questionnaire Core-30

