### Criteria for re-administration/cycle delay

Patients who meet all of the following criteria can receive the planned treatment:Absolute neutrophil count (ANC) > 1500/mm^3^Platelets > 100,000/mm^3^Treatment related to non-hematologic toxicity has been eliminated at baseline or is at a level ≤ 1 (except for level-2 alopecia or level-2 fatigue)

If the patient cannot meet these criteria, the planned treatment will be delayed and the patient’s condition will be re-evaluated at least once a week.

Additional criteria for re-administration/cycle delay are as follows:The medication on the 8th day of each cycle cannot be delayed for longer than 1 week, otherwise, the patient will be withdrawn from the study. The time of medication administration in the next cycle will not change.In the case of failure to recover from treatment-related toxicity to baseline or level 1 (except level 2 and level-2 fatigue) within 3 weeks as scheduled (i.e., the start of each new cycle is delayed for over 21 days as compared with the scheduled time), the patient will be withdrawn from the trial.Patients can continue to use the drug, with the consent of the Sponsor, if the treatment is deemed to be effective.

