### Participant withdrawal

Patients will be withdrawn from the study if they (1) withdraw their informed consent; (2) request to withdraw from the trial; or (3) decline to continue treatment or follow up. All source data and source files related to all withdrawn participants will be retained. The time and cause of withdrawal will be recorded on the case report form in detail.

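### Two different cycle-delay limits (at least 2 weeks, and over 21 days) decide who must leave, and the exit is worded as leaving the trial rather than stopping treatment

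*Protocol article*

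**What the plan says.** Two sections of the protocol article set an exit rule for a late next cycle.

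- **Dose adjustment:** patients "having a delay of the subsequent treatment cycle of at least 2 weeks, will be required to withdraw from the trial". The same section has a separate limit for interruptions inside a cycle: "The time for each pause and the cumulative time of overall pauses per cycle are limited to 1 week".
- **Criteria for re-administration/cycle delay:** if toxicity has not resolved and the start of a new cycle "is delayed for over 21 days as compared with the scheduled time), the patient will be withdrawn from the trial". While a cycle is on hold, the patient's "condition will be re-evaluated at least once a week". The last item in that list reads: "Patients can continue to use the drug, with the consent of the Sponsor, if the treatment is deemed to be effective".

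The Participant withdrawal section gives three patient-initiated grounds for withdrawal from the study. One of them covers patients who "decline to continue treatment or follow up", so stopping drug and stopping observation are joined in a single ground.

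Other places point to observation after drug stops. The Fig. 1 legend says "follow up for survival will be monitored every 3 months after treatment discontinuation until patient death or study completion". The Follow up section lists disease progression, new anticancer treatment and survival status at each 3-monthly contact. The Primary outcome section applies RECIST in follow-up as well as on treatment.

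**The concern.** There are two linked problems.

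First, staff facing the same toxicity delay have two written instructions that disagree over a definite range. One tells them to take the patient out; the other does not. The sponsor-consent sentence adds discretion without saying which limit it relaxes.

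Second, the exit is worded as leaving the trial or study, not as stopping study drug. Someone who follows that wording literally stops collecting progression and survival data. The patients affected are not a random subset: they leave because of toxicity or because they decline further treatment. Only one arm receives apatinib, so toxicity exits could plausibly be uneven between arms.

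The PFS definition makes this matter. It counts the start of another systemic or targeted anti-tumour therapy as an event. A patient who exits for toxicity and then starts other therapy has a PFS event if still observed, and missing data if treated as gone. The Statistical analysis section plans conservative imputation of missing primary endpoint data, but imputation does not replace an observed progression or death.

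**Working it through.** The protocol gives no figure to reproduce here. The check sets the rules side by side.

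**Step 1. Do the two limits govern the same event?** The Dose adjustment section has its own 1-week cap on pauses within a cycle and treats lateness of the following cycle separately. The re-administration section also concerns lateness of a new cycle, after failure to recover from treatment-related toxicity. Both therefore apply to a next cycle held up by toxicity, and neither cites the other or says which prevails.

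**Step 2. Where do they disagree?**

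| Delay of next cycle | Dose adjustment | Re-administration/cycle delay |
|---|---|---|
| Under 14 days | no exit | no exit |
| 14 to 21 days | must leave | no exit |
| Over 21 days | must leave | must leave, unless the sponsor exception applies |

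The disputed range is 21 − 14 + 1 = 8 daily values. If the weekly re-evaluations are counted from the scheduled start, the checks at days 14 and 21 both fall inside it.

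**Step 3. Is the range likely to be reached?** The protocol gives no rate of delay. Delays are foreseeable, however: eligibility admits platelets from 80 × 10^9/L, while planned treatment needs more than 100,000/mm^3, which is 100 × 10^9/L.

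**Step 4. What does the sponsor exception cover?** It stands at the end of the re-administration list and names no limit. It could lift the 21-day rule, the other exit rule in that list, or the 2-week rule in the other section. The text does not decide.

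**Step 5. What does the exit end?** Both delay rules have the patient leave the trial. The Participant withdrawal section has patients who decline treatment withdrawn from the study. None of the three says that drug stops while observation continues. The follow-up provisions are triggered by treatment discontinuation, and they do not say whether a patient withdrawn under a delay rule is covered. Intent points to yes; the literal exit wording points to no.

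**Step 6. Can the effect be sized?** Not from the document. It gives no rate of toxicity exit, no split by arm and no prognosis for such patients. The 10% dropout in the Sample size section is not broken down by cause.

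**The case against.** The strongest reply is that the protocol as a whole means follow-up to continue. The Study design section has allocated treatment run until progression or until other criteria call for drug to be ended, which frames criterion-driven exits as the end of drug. The Participant withdrawal section does not list the delay rules. Post-treatment follow-up runs to death or study completion with no exception for toxicity exits, and the Adverse events section presupposes observation after the last dose. This stands. A reader might infer that follow-up certainly ends for these patients, and the documents do not support that. What remains is exit wording that says the opposite of the apparent intent.

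It can also be said that the Dose adjustment rule concerns apatinib toxicity while the other covers planned treatment generally, that the latter does not expressly permit a delay of 14 to 21 days, and that staff could comply with both by using the stricter limit. The last is true, but the 21-day rule would then have no effect, which cannot be what was meant.

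Four further inferences are tempting and should not be drawn:

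- **A conflict with intention-to-treat.** The Statistical analysis section defines ITT as analysis by allocated group. Early exit does not contradict that; informative loss is a different matter.
- **Missing follow-up imaging.** The prose list names no scan, but it does name disease progression, the Abstract's scan schedule is not tied to being on drug, and the schedule figures are not shown. A condensed list is not evidence of an omission.
- **The day-8 rule as a further error.** The sentence "The medication on the 8th day of each cycle cannot be delayed for longer than 1 week, otherwise, the patient will be withdrawn" is awkward for a continuous schedule, but day 8 is a dosing day and the 1-week limit is compatible with the pause cap.
- **A loss of power.** Nothing in the document ties these exits to a number of lost events.

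**Conclusion.** The point holds in two parts of different strength. The conflict between the limits is certain on the text: delays of 14 to 21 days inclusive receive opposite instructions, with a sponsor exception of unstated scope. The risk to the endpoints is conditional. It arises only if the exit wording is followed literally, and then patients who stop for toxicity or decline treatment could be lost informatively from PFS and OS. That exits might be uneven by arm is an assumption, resting only on apatinib being given in one arm. Neither the size nor the direction of any bias can be stated. The protocol should be corrected because the contradiction is plain and the remedy is cheap, not because harm has been shown.

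**What to change.** 1. State one limit for delay of the next cycle, in the same words, in both the Dose adjustment section and the re-administration section. Whether it is 2 weeks or 21 days is a clinical choice.
2. Say whether the sponsor-consent exception applies to that limit.
3. In both sections, and for declining treatment in the Participant withdrawal section, replace the wording about leaving the trial or study with: *discontinue study treatment; scheduled tumour assessment until progression and survival follow-up continue unless consent to follow-up is withdrawn*. Keep refusal of follow-up as a separate ground.

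The cost is an amendment with ethics committee approval, plus continued scans until progression and 3-monthly contacts for patients who stop treatment early. The sample size does not change.

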**Drug withdrawal**	
Neutrophil	Level 3 or 4
Platelet	Level 3 or 4
Serum creatinine	1.5 times over the upper limit of normal value (44–132 μM)
Infection	Infectious fever with temperature > 38 °C
Diarrhea, mouth ulcers	Level 3 or 4
Others	When adverse reactions occur in addition to the above, and the investigators cannot judge whether drug administration can be continued or not, the drug will be discontinued
**Drug re-administration**	
Neutrophil	> 1.0 × 10^9^/L
Platelet	> 50 × 10^9^/L
Serum creatinine	< the upper limit of normal value (44–132 μM)
Infection	No infectious fever
Diarrhea, mouth ulcers	≤ Level 1
Others	When adverse reactions leading to drug withdrawal are alleviated or disappear, the administration can be resumed as determined by the investigators

Drug withdrawal and re-administration will be assessed using the National Cancer Institute Common Toxicity Criteria (NCI-CTC) Version 4^30^

### Concomitant medications

Conventional medications will be given to address patient symptoms. These may include prophylactic antiemetics and treatment with granulocyte colony-stimulating factor (as indicated by the patient’s hemogram). Hematopoietic growth factor support is permitted to avoid treatment interruption or delay. All symptomatic medications will be documented and detailed on a case report form.

### Assessment

#### Baseline evaluations (conducted within 2 weeks of the start of protocol therapy)

We will collect baseline data as follows:Demographic dataAmerican Joint Committee on Cancer tumor diagnosis and stagingRelevant clinical disease history (diagnosis and treatment)Concomitant medicationPhysical examinationVital signsECOG-PS scoreImaging (computed tomography (CT) or magnetic resonance imaging (MRI))ElectrocardiogramLaboratory tests: routine blood test, liver and kidney functional electrolytes (including K^+^, Na^+^, Cl^−^, Ca^2+^, Mg^2+^)Tumor markers: CA153, carcinoembryonic antigen (CEA)Pregnancy test (if necessary)The European Organization for Research and Treatment of Cancer Quality of Life Questionnaire Core-30 (EORTC QLQ-C30, version 3)

#### During treatment (conducted every 6 weeks (two cycles))

During treatment we will collect data on the following:Physical examinationVital signsECOG-PS scoreImaging test (CT or MRI)Laboratory tests: routine blood test, liver and kidney functional electrolytes (including K^+^, Na^+^, Cl^−^, Ca^2+^, Mg^2+^)Tumor markers: CA153, CEAEORTC-QLQ-C30 version 3 scoreAdverse reactions, concomitant medications

#### Follow up

At 4 weeks after treatment discontinuation we will collect data on the following:Physical examinationVital signsECOG-PS scoreLaboratory tests: routine blood test, liver and kidney functional electrolytes (including K^+^, Na^+^, Cl^−^, Ca^2+^, Mg^2+^)Tumor markers: CA153, CEAEORTC-QLQ-C30 version 3 scoreAdverse reactionsConcomitant medications (opioid analgesic consumption and new anticancer treatment)

Every 3 months after treatment discontinuation, until the patient dies or reaches study completion, we will collect data on the following:ECOG-PS scoreNew anticancer treatment(s)Disease progressionSurvival status

### Outcomes

#### Primary outcome

PFS refers to the length of time from randomization and group allocation to any recorded tumor progression (including tumor recurrence, presence of new lesions, tumor treatment, and the use of other systemic or targeted anti-tumor therapies) or death (due to any cause). If the patient has several indicators that can be judged as progression of disease, the PFS analysis will be performed based on the indicator that first emerged. For patients with no tumor progression and who are still alive by the end of the study, the PFS time recorded at the last follow up will be censored. Tumor conditions during the treatment and follow-up periods will be evaluated in accordance with the RECIST version 1.1 criteria.

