**Methods/analysis:**

This study is a triple-blind, randomized, placebo-controlled, parallel-group clinical trial. We plan to include 238 female patients with locally recurrent or metastatic TNBC, admitted to the Liaoning Cancer Hospital & Institute, Northeast China. All enrolled patients will be randomized to oral vinorelbine alone (40 mg, thrice a week (Mondays, Wednesdays, and Fridays) in each 3-week cycle), or in combination with oral apatinib mesylate (500 mg, once daily in each 3-week cycle). Radiographic assessment will be performed every 6 weeks for 36 weeks and every 9 weeks thereafter. The primary outcome is progression-free survival and secondary outcomes include overall survival, disease control rate, objective response rate, and incidence of adverse events at grades 3 and 4, as defined by the National Cancer Institute Common Toxicity Criteria Version 4.0. Outcome measures will be evaluated at baseline (< 2 weeks before starting treatment), every 6 weeks during treatment, and at 4 weeks and every 3 months after treatment discontinuation.

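### PFS is censored at the last follow-up contact, which need not include a scan, and the stated imaging schedules contradict one another

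*Protocol article*

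**What the plan says.** **Endpoint (Primary outcome).** "PFS refers to the length of time from randomization and group allocation to any recorded tumor progression" or death. Recorded progression is defined to include "tumor treatment, and the use of other systemic or targeted anti-tumor therapies". For patients without progression "who are still alive by the end of the study, the PFS time recorded at the last follow up will be censored". The next sentence adds: "Tumor conditions during the treatment and follow-up periods will be evaluated in accordance with the RECIST version 1.1 criteria".

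**After treatment (Follow up).** The 4-week visit lists examination, vital signs, performance status, laboratory tests, tumour markers, quality of life, adverse reactions and concomitant medication, but no imaging. Then: "Every 3 months after treatment discontinuation, until the patient dies or reaches study completion, we will collect data on the following". Four items follow: performance status, new anticancer treatment, disease progression and survival status. Imaging is again absent. The legend of Fig. 1 describes these 3-monthly contacts as follow-up for survival.

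**On treatment.** Three statements bear on timing:
- Abstract, Methods/analysis: "Radiographic assessment will be performed every 6 weeks for 36 weeks and every 9 weeks thereafter".
- Assessment, under the heading "During treatment (conducted every 6 weeks (two cycles": the list includes CT or MRI, with no change of interval at week 36.
- Drug administration: "An assessment will be conducted at the end of every second cycle of the described administration protocol".

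**The concern.** A patient is known to be progression-free only up to her last tumour assessment. A later contact without a scan shows that she is alive and what she or the site reports. Censoring at that contact counts the interval since the last scan as progression-free. The date would suit overall survival; for PFS it does not.

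The schedule adds to this. If scans follow the treatment visits, a patient who stops drug before progression moves from 6-weekly imaging to 3-monthly contacts with no listed scan. If scans follow cycles, a delayed cycle delays the scan. Only one arm receives active apatinib on top of vinorelbine, so unequal stopping or delay is a realistic possibility, and blinding does not prevent it. The log-rank comparison on the primary endpoint would then compare arms observed differently.

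**Working it through.** **1. The sections side by side**

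| Period | Where stated | Tumour assessment |
|---|---|---|
| Baseline | Baseline evaluations | CT or MRI listed |
| On treatment | During treatment | CT or MRI every 6 weeks (two cycles) |
| On treatment | Drug administration | An assessment after every second cycle |
| Not limited to treatment | Abstract | 6-weekly to week 36, then 9-weekly |
| 4 weeks after stopping | Follow up | None listed |
| Every 3 months after stopping | Follow up; Fig. 1 legend | None listed; progression recorded as an item |
| Follow-up period | Primary outcome | RECIST 1.1 evaluation promised |

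These cannot all be followed. The abstract and the treatment list part at week 36. The RECIST promise has no listed post-treatment scan behind it. Two cycles equal 6 weeks only if no cycle is delayed, and delays are allowed for. (Dose adjustment sets withdrawal at a cycle delay of at least 2 weeks, the re-administration criteria at over 21 days; those passages also need reconciling, and no view is taken on which is right.)

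**2. Who reaches the point where the two schedules part**

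Inputs: design medians of 4.1 and 6.7 months (Sample size); exponential PFS assumed. Week 36 is 252 / 30.44 = 8.28 months. S(t) = 2^(−t/median):
- control: 2^(−8.28/4.1) = 0.25
- experimental: 2^(−8.28/6.7) = 0.42

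Applied equally to both arms, however, 6-weekly scanning throughout gives a simulated hazard ratio of 0.639, against 0.643 for 6- then 9-weekly. The conflict alone barely matters to the estimate.

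**3. How many patients reach the end without an event**

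With uniform accrual over 26 months and 15 months of follow-up, P(event) = 1 − [exp(−15λ) − exp(−41λ)] / (26λ), where λ = ln 2 / median:
- control, λ = 0.1691: 1 − (0.0792 − 0.0010)/4.396 = 0.982
- experimental, λ = 0.1035: 1 − (0.2119 − 0.0144)/2.690 = 0.927

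The average is 0.954. About 5% would be censored if every event were found when due.

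**4. What unequal stopping or delay could do when there is no true effect**

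The protocol gives no stopping or delay rates, so all rates below are assumptions. Both arms have a 4.1-month median; scans are 6-weekly (1.38 months) on treatment. Stopping rates are control vs experimental.

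| Handling after stopping | Assumed stops | Hazard ratio |
|---|---|---|
| Calendar scans continue | 5% vs 20% | 1.00 |
| Progression found at 3-monthly contacts, new therapy ignored | 5% vs 20%; 10% vs 30% | 0.98; 0.97 |
| Unimaged until death (mean 8 months later), new therapy ignored | 5% vs 15%; 10% vs 25% | 0.93; 0.89 |
| As above, with 50% of stoppers starting new therapy (mean 1–2 months after stopping), counted as an event | same | 0.99–1.01 |
| As above, with 80% starting new therapy | same | 1.05–1.10 |
| Found at 3-monthly contacts, 50–80% starting new therapy | same | 1.05–1.14 |

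A separate run of the 3-monthly case gave 0.99.

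An artificial extreme isolates the censoring date. Suppose that progression after stopping is never found, and deaths and new therapy are ignored. With 5% vs 20% stops, censoring at last contact gives 0.68 and censoring at last scan gives 1.00, if stopping is unrelated to prognosis. The protocol's endpoint cannot reach that extreme, because death and new therapy are events.

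If delays stretch one arm's scans at every interval to 7, 8 or 9 weeks, the hazard ratio is 0.95, 0.94 or 0.91.

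**The case against.** The best reply is that the plan does intend tumour evaluation after treatment. The sentence after the censoring rule says so, the abstract's calendar schedule is not confined to treatment, and progression is an item at every 3-monthly contact. On that reading one visit list in a condensed article omits a scan. The grids in Figs. 1 and 2 were not available for this check. Moreover, death and new therapy are PFS events, so patients who stop drug are not simply lost to the endpoint; few patients are censored; the section that ties an assessment to cycles does not mention imaging; and a shared schedule gives nearly the same hazard ratio either way.

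All of this stands, and it limits the size. It also means the document should not be read as planning no imaging after discontinuation: it is a contradiction between sections. It does not rescue the censoring date, which is stated explicitly and is not tied to an assessment. Nor does it tell a site which schedule to follow. The promise in Statistical analysis to impute missing primary endpoint data conservatively does not clearly reach these patients, since the stated rule gives them a censored time.

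**Conclusion.** The point holds as a wrongly stated censoring date together with contradictory imaging schedules for the primary endpoint. As written, unassessed time can count as progression-free, and ascertainment can change when a patient stops or delays treatment.

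A bias in the hazard ratio needs stopping or delay to differ by arm or to relate to prognosis. A reader might infer that the rule favours apatinib and inflates the false-positive rate. The document does not support that. The result is about 0.9 only if progression goes unimaged until death and new therapy is ignored; it is 0.97 to 0.99 if the 3-monthly progression item works; and it is about 1 or above once new therapy counts as the event that the protocol makes it. Direction and size therefore stay open. The schedule conflict on its own is a matter of clarity, not a material source of bias.

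**What to change.** 1. In Primary outcome, censor patients without a PFS event at the date of the last adequate tumour assessment, or at randomisation if there is none.
2. Reconcile the abstract, Drug administration, During treatment, Follow up and Primary outcome sections, and the Fig. 1 legend, into one imaging schedule. Time it in calendar weeks from randomisation and continue it to RECIST progression whether or not study drug continues. List the scan in the post-treatment visits.

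The second change matters more. Censoring at the last scan is unbiased only if stopping is unrelated to prognosis, and scans not taken cannot be recovered later. Neither change alters how new therapy is counted, which is a separate question.

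The cost is wording, scans for the minority who stop drug before progression, and slightly more censored time.
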